**Abstract**

**Background:** There is no consensus on the ventilation management during cardiopulmonary bypass (CPB), and the anesthesiologists or the surgeons usually ventilate the lungs with different ventilation strategies or keep them static. Better outcomes are more likely to occur when the ventilation is administered during CPB according to the existing literatures. However, the use of high fraction of inspired oxygen (FiO_2_) is debatable in cardiac surgery. And the potential effects of strategies combining low tidal volume (V_T_) ventilation with different FiO_2_ during CPB on postoperative pulmonary complications (PPCs) are unclear.

**Design:** The VONTCPB trial is a single-center, prospective, double-blinded, randomized, controlled trial. We are going to recruit total 420 elective cardiac surgery patients with median sternotomy under CPB, who will be equally randomized into three different ventilation strategy groups: NoV, LOV and HOV. (1) The NoV group receives no mechanical ventilation during CPB; (2) the LOV group receives a low V_T_ of 3-4ml/kg of ideal body weight (IBW) with the respiratory rate (RR) of 10-12 acts/min, and the positive end-expiratory pressure (PEEP) of 5-8 cmH_2_O during CPB; the FiO_2_ is 30%; (3) the HOV group receives a low V_T_ of 3-4ml/kg of IBW with the RR of 10-12 acts/min, and the PEEP of 5-8 cmH_2_O during CPB; the FiO_2_ is 80%. The primary endpoints are the incidence of the composite of PPCs and the PPCs score. The secondary endpoints refer to the incidence of the oxygenation index (PaO_2_/FiO_2_ ratio) <300 mmHg at three time points (the moment arriving in the ICU, 6 and 12 hours after arrival in the ICU), the surgical incision healing grade, the intubation time, the stay of ICU, the length of hospital stay, and mortality at 30 days after the surgery.

**Discussion:** The VONTCPB trial is the first study to assess the effects of strategies combining low tidal volume (V_T_) ventilation with different FiO_2_ during CPB on patients’ outcomes.

**Trial registration:** ChiCTR1800015261. Registered on 20 March 2018.

**Keywords:** Cardiopulmonary bypass, Low tidal volume, Mechanical ventilation，Oxygen concentration, Postoperative pulmonary complications,.

**Background**

Surgical and anesthesia techniques of heart surgery have been greatly improving. However, the postoperative pulmonary complications (PPCs) are still the main complications after surgery, resulting in increasing mortality in cardiac surgery with the incidence of 25% [1]. The PPCs have the forms of respiratory failure, respiratory infection, pleural effusion resulting in thoracentesis, atelectasis, pneumothorax, bronchospasm, aspiration pneumonitis [2]. These complications extend the length of mechanical ventilation and intensive care unit (ICU) stay, indicating worse prognosis [3, 4].

The etiologies of the PPCs are quite complicated. Lungs are isolated from the artificial extracorporeal circulation, which results in blood supply to the lungs only from the bronchial arteries. While two sets of independent circulation systems composing the blood delivery system of the lungs, the bronchial arteries supply only about 3-5% of the pulmonary blood flow system, which may be reduced to one-tenth of the original upon experimental conditions of CPB in pigs model. Those reduced blood flow may be difficult to meet the physiological metabolic needs of the lungs [5]. The tissue of the lungs is also very loose, vascular fluid can be easily transferred to the interstitial tissue under pathologic conditions. Those factors, in addition to the strikes of pulmonary ischemia-reperfusion and reoxygenation, oxygen-free radicals, inflammatory response make the lungs especially vulnerable in the dedicated phases [4].

Perioperative hyperoxia has been declared to bring some benefits. As is known to us all, the increase in the arterial blood partial pressure of oxygen (PaO_2_) could compensate the adverse effects of a reduction in cardiac output on tissue oxygenation. In addition, 80% fraction of inspired oxygen (FiO_2_), hyperoxia can increase the activity of antioxidative enzymes and reduce the oxidative stress induced by ischemia and reperfusion acting similarly to the effect of ischemic preconditioning, thus exerts an active therapeutic effect on organ ischemia-reperfusion injury [6, 7]. However, studies have suggested that hyperoxia associated lung injury and its possible mechanisms [8]. A review suggested that the best usage of hyperoxia is in the timing [9]. Anyway, the debate is still on going.

The common practice of respiratory management during CPB is to suspend the ventilation [10]. Re-expansion pulmonary edema occurs during a long-period collapsed pulmonary reopening, resulting in the reduced lung compliance and ventilation perfusion ratio imbalance [11]. Continuous ventilation during CPB may somehow reduce the pulmonary edema and inflammation. However, the setting of the ventilation parameters is the work of art. A lot of randomized controlled trials (RCTs) were designed to investigate the influence of different ventilation strategies during CPB on the outcomes in heart surgery patients [12-27]. All these RCTs have their own limits. Though the evidence is weak, it still suggests that maintaining mechanical ventilation during CPB is beneficial to lung protection.

The recent meta-analysis made by our research team shows that the ventilation of the resting lung during CPB is indeed effective in improving the oxygenation (PaO_2_/FiO_2_ ratio) and gas exchange. This approach can also reduce the alveolar-arterial oxygen partial pressure difference and the intrapulmonary shunt. But it is unclear of its effect on the long-term prognosis and outcomes for patients. The authors pointed that different FiO_2_ and other respiratory parameters settings may impact the long-term outcomes [28]. An earlier meta-analysis summarized the publications of different ventilation strategies during CPB. Using continuous positive airway pressure (CPAP) and lung recruitment maneuvers can increase oxygenation immediately after CPB to a certain extent, but there is no evidence of a sustained effect [29]. A just published systematic review and meta-analysis concluded that CPAP during CPB may improve the oxygenation and gas exchange while ventilation did not. The authors mentioned that the FiO_2_ had been ignored for a long period [30]. Heinrichs et al [31] reviewed the RCTs to investigate the impact that hyperoxia has on postoperative organ dysfunction, length of stay, and mortality during adult cardiac surgery. They concluded that the impact of hyperoxia on these outcomes seems to be minimal because of the high heterogeneity of include studies. Similarly, McGuinness et al [32] failed to demonstrate any difference in AKI, markers of organ damage, or length of stay by comparing the avoidance of arterial hyperoxemia versus usual care during CPB.

There is no generally accepted ventilation management model due to weak evidence of heterogeneity researches [10, 33, 34]. Therefore, we designed a prospective RCT combining the different regimens of ventilation settings during CPB with low or high FiO_2_ to explore the optimal ventilation mode during CPB.

**Objectives**

We designed this RCT to compare the clinical effects of three mechanical ventilation strategies on the total incidence of PPCs during postoperative hospitalization. We chose the incidence of composite PPCs as the primary outcome because it is a hard parameter. While in the past many studies only focused on observing biochemical indicators or indirect parameters. You could never tell whether those indicators in the blood have sustained influences in the long run or not. It could be just a transient change after surgery. We hope we would reach a conclusion of optimal ventilation management during CPB, and finally we could make a difference in the clinical practice.

**Methods/design**

The VONTCPB study is a single-center, double-blinded, three-armed, randomized controlled trial comparing three mechanical ventilation strategies (NoV, LOV and HOV) during CPB in adult patients undergoing cardiac surgery. The protocol structure is written according to the Consolidated Standards of Reporting Trials (CONSORT) 2010 Statement guidelines and follows the Standard Protocol Items: Recommendations for Interventional Trials (SPIRIT) Statement. The SPIRIT checklist can be found in Additional file 1. The SPIRIT figure is illustrated in ***Figure 1***.

**Ethical approval and trial registration**

This clinical study protocol has been approved by the Biomedical Research Ethics Committee of West China Hospital of Sichuan University on 12 March 2018 (Approval number 2017 （400）) and registered in the Chinese Clinical Trials Registry (ChiCTR) ([www.chictr.org.cn](http://www.chictr.org.cn/)) with the registration number ChiCTR1800015261 on 19 March 2018.

**Participants**

The patients included in the trial must be more than 18 years old and undergo elective cardiac surgery with median sternotomy under CPB. Simultaneous other non-cardiac surgery procedure is excluded. The inclusion and exclusion criteria are shown as below:

Inclusion criteria:

- Age ≥18 years
- Signed informed consent
- Elective cardiac surgery patients with median sternotomy under CBP

Exclusion criteria:

- Pregnant women
- Heart transplantation,
- Pulmonary thromboendarterectomy
- Aortic arch and other deep hypothermic circulatory arrest surgery
- Long-term use of hormone therapy before surgery (≥3 months)
- Participated in other similar researches 3 months ago

**Endpoints**

The primary endpoints are the incidence of a composite of PPCs and the PPCs score during hospital stay [35-37]. The detailed definitions of PPCs are shown in ***Table 1***. The score is presented in ***Table 2***. Secondary endpoints are listed as follows: the incidence of oxygen index <300 mmHg at three time points (the moment arriving in the ICU, 6 and 12 hours after arrival in the ICU), the surgical incision healing grade, the intubation time, the length of ICU stay and hospital stay, and postoperative 30-day mortality rate.

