**Statistical considerations**

**Sample size**

Sample-size calculation is based on two-sided alpha error of 0.05 and 80% power. We performed a pilot-study, showing that the P_max_ is 40% in the LOV group (15 patients) and the P_min_ is 22% in the NoV group (14 patients). Therefore, we expect a reduction of 45% in the incidence of this parameter, and then calculate the sample size of 127 patients per group (381 in total). Considering a dropout fraction of 10%, we will finally need a total of 420 participants.

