**Data analysis**

Data will be analyzed following the intention-to-treat principle using SPSS version 22.0 (SPSS, Chicago, IL, USA). Comparisons in the dichotomous variables will be made by the chi-square tests (or Fisher exact tests where numbers are small). Comparisons in the continuous variables will be made by analysis of variance or the nonparametric Kruskal-Wallis H test. Two-sided significance tests will be used throughout. The Results will be presented as n (%), mean (SD), or median (interquartile range). Bonferroni correction will be used when doing post hoc analysis.

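### The Objectives name one primary outcome, the Abstract and Endpoints sections name two, and the protocol does not say how the two relate

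*Protocol*

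**What the plan says.** Three parts of the protocol speak of primary endpoints in the plural. The Endpoints section says "The primary endpoints are the incidence of a composite of PPCs and the PPCs score during hospital stay". The Abstract says "The primary endpoints are the incidence of the composite of PPCs and the PPCs score". The Discussion also uses the plural, without listing them.

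The Objectives speak in the singular: "We chose the incidence of composite PPCs as the primary outcome because it is a hard parameter".

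The Sample size section says "Sample-size calculation is based on two-sided alpha error of 0.05 and 80% power". It then derives 127 patients per group from a highest pilot rate of 40% and a lowest of 22%. It does not name the parameter, but the figures are proportions, so they cannot be the graded PPCs score.

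The only multiplicity rule is in Data analysis: "Bonferroni correction will be used when doing post hoc analysis". With three arms, this most naturally means pairwise comparisons after an overall test. It does not mention the two primary endpoints.

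**The concern.** The number of primary endpoints is stated in the protocol itself, and stated in two ways. A separate analysis plan could set a testing order, but it could not comply with both the Objectives and the Endpoints section.

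Two things are at stake. One is which result decides the trial when the endpoints point in different directions. The other is whether the stated operating characteristics hold. Under one reading of two primaries the 5% error rate fails; under the other the 80% power is unsupported.

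**Working it through.** **1. What the stated sample size covers.** Inputs from the Sample size section: rates 0.40 and 0.22, two-sided alpha 0.05, power 80%. The rate in the third arm is not given; assume the midpoint, 0.31.

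- Three-group chi-square, 2 df: the noncentrality needed for 80% power at 0.05 is 9.635.
- Mean rate = 0.31. Effect per patient in each arm = [(0.40 − 0.31)² + (0.22 − 0.31)² + (0.31 − 0.31)²] / (0.31 × 0.69) = 0.0162 / 0.2139 = 0.0757.
- n per group = 9.635 / 0.0757 ≈ 127.2 (unrounded effect), against the stated 127.
- The arcsine version, 9.635 / [2(asin√0.40 − asin√0.22)²], gives 124.7, so 125.
- Total: 3 × 127 = 381; 381 × 1.10 = 419.1, stated as 420.

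The plan's figure therefore reproduces as one endpoint tested across three arms at the full 0.05.

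**2. If a win on either endpoint at 0.05 counted.** Under independence the family-wise error is 1 − 0.95² = 0.0975. For related endpoints, two 2-df chi-square statistics were simulated (1,000,000 draws) with correlation r between their normal components. The protocol gives no correlation, so r is an assumption.

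| Assumed r | Error rate for either endpoint | Ratio to 0.05 |
| --- | --- | --- |
| 0 (exact) | 9.75% | 1.95 |
| 0.5 | 9.2% | 1.8 |
| 0.7 | 8.5% | 1.7 |
| 0.9 | 7.2% | 1.4 |
| 0.95 | 6.5% | 1.3 |

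**3. If both endpoints were required.** Rejecting both is never more likely than rejecting either one alone, so the type I error is at most 5%. By the same logic, joint power is at most the power for the incidence: 79.9% at 127 per group, or 83.9% if all 140 per group contributed. The protocol gives no effect size for the score. If the score also had 80% power (an assumption), joint power would lie between 0.80 + 0.80 − 1 = 60% and 80%.

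**4. If alpha were split, 0.025 each.** The noncentrality becomes 11.493, and 11.493 / 0.0757 ≈ 151.8, so 152 per group or 456 in total. At 127 per group, power for the incidence falls from 80% to 71%.

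**5. Can the endpoints disagree?** Table 1 (composite) and Table 2 (score) side by side:

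- Pleural effusion: x-ray evidence is enough in Table 1. Table 2 grades an effusion only when it led to thoracentesis.
- Dry cough: Grade 1 in Table 2, absent from Table 1.
- Death before discharge: Grade 5 in Table 2, absent from Table 1.

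A significant result on one endpoint and a null result on the other is therefore possible, and the protocol has no rule for it.

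**The case against.** - **A reader might infer that the risk of a false claim is nearly doubled.** The documents do not support that. The factor of 1.95 needs independent endpoints and a rule that either one suffices, and the protocol states no such rule. Tables 1 and 2 share atelectasis, bronchospasm, pneumothorax, effusion, hypoxaemia and respiratory infection or pneumonia in the same patients and hospital stay. Positive correlation is to be expected, and the inflation is then smaller.
- **A reader might infer that the deciding endpoint cannot be known at all.** That also goes too far. The Objectives justify the composite and the sample size rests on an incidence, so both point the same way. What stands is that the sections defining the endpoints say otherwise.
- **Testing order and alpha allocation are often left to an analysis plan, which is not shown here.** This is fair, and the absence of a hierarchy alone would not be a fault. The conflict over the number of primary endpoints is in the protocol and remains.
- **Alpha may have been halved without saying so.** A two-arm comparison of 40% with 22% at 0.025 gives 125 per group, close to 127. But the section states 0.05 and no split, and the three-arm calculation at 0.05 matches more closely.
- **A yes/no incidence and a graded score are different instruments, so some divergence is no error.** Agreed; it matters only because both are called primary. Nor should the disagreement be overdrawn. It is tempting to say that a PaO2/FiO2 of 250 counts in Table 1 and scores nothing in Table 2. On room air it means a PaO2 of 0.21 × 250 = 52.5 mmHg, which would ordinarily meet the Grade 2 hypoxaemia criterion. The effusion and dry-cough examples do not have this difficulty.

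**Conclusion.** The protocol contradicts itself on how many primary endpoints it has, and it sizes the trial for one. That part rests on the text alone and needs no assumption.

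The numerical consequence is conditional. It is an error rate above 5% if either endpoint suffices, up to the independence figure in the table, or a joint power below the stated level in general if both are required. If the Objectives govern, neither problem arises and the stated alpha and power apply as written. The correlations, the third-arm rate and the power for the score are assumptions. The contradiction should be removed before outcome data are analysed, because until then the choice between the readings could be made after seeing the results.

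**What to change.** Follow the Objectives.

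- **Abstract and Endpoints:** name the composite PPC incidence (Table 1) as the single primary endpoint, and list the PPCs score (Table 2) as the first secondary endpoint.
- **Data analysis:** state that the composite is tested across the three arms at two-sided 0.05, and that the score is tested at 0.05 only if the composite is significant. Say that the existing Bonferroni rule applies to the comparisons between arms.
- **Sample size:** name the composite incidence as the parameter used.
- **Discussion:** change the plural to the singular.

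Alpha stays at 0.05 and the sample size at 381, or 420 with dropout. The cost is wording, plus the loss of the score's independent confirmatory claim.

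If the sponsor wants both endpoints to carry a claim, an equal split is also valid. It needs 456 patients before dropout (456 / 0.9 = 507 after), or acceptance of the lower power for the incidence at 127 per group.

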**Randomization/Blinding**

The random number table was generated by Microsoft Excel in a 1:1:1 treatment ratio. The investigator who is responsible for grouping visits the patients the day before surgery and gets the consents. Once the patient is qualified, he determines the serial number and random number of the patient and writes on the Case Report Form (CRF). He will also inform the anesthesia care providers who do not participate in the study the treatment of the patient. The patient, the data collector and the intensivist are not aware of the treatment information in the whole process. Any intraoperative event (such as pleura incision) or deviation from the protocol is recorded on the CRF.

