**Data collection**

All the related data are collected on the CRF. Preoperative data include age, height, weight, EuroSCORE Ⅱ, smoking status, diabetes mellitus, peripheral arterial disease, pulmonary comorbidity, pulmonary infection in the past 30 days and the classification of American Society of Anesthesiologists (ASA). Intraoperative data include type and duration of surgery procedure, duration of CPB and aortic cross clamp, units of allogeneic red blood cell transfusions, volume and type of fluids administered. Postoperative data include time to extubation, need for non-invasive ventilator, re-intubation, postoperative hospital stay, temperature, leukocyte count and chest X-ray. Other data at three time points (the moment arriving in the ICU, 6 and 12 hours after arrival in the ICU) include PaO_2_, FiO_2_, and partial pressure of carbon dioxide (PaCO_2_). PPCs events are traced throughout the hospitalization.

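### The investigator who obtains consent also assigns the random number and knows the treatment, and the protocol describes nothing that hides the next assignment from him

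*Protocol*

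**What the plan says.** All of the allocation procedure is in the protocol's Randomization/Blinding section.

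- Source of the sequence: "The random number table was generated by Microsoft Excel in a 1:1:1 treatment ratio". The section does not say who made, keeps or can view the table.
- Consent: "The investigator who is responsible for grouping visits the patients the day before surgery and gets the consents".
- Assignment: "Once the patient is qualified, he determines the serial number and random number of the patient and writes on the Case Report Form (CRF".
- Communication of the arm: "He will also inform the anesthesia care providers who do not participate in the study the treatment of the patient".
- Blinding: "The patient, the data collector and the intensivist are not aware of the treatment information in the whole process".
- Other CRF content: "Any intraoperative event (such as pleura incision) or deviation from the protocol is recorded on the CRF".

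The Data collection section adds: "All the related data are collected on the CRF". The Methods/design section says that the protocol follows CONSORT and SPIRIT.

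**The concern.** Randomization protects the comparison only if the person deciding whether to enroll a patient cannot know what that patient would receive. Here the person who sees the patient and takes consent also does the grouping. If he can see the next entry, he can pass over or postpone a patient who seems a poor match for it. Surgery is elective, so deferral is feasible. The inclusion criteria admit a broad range of adult bypass surgery, so risk of pulmonary complications will differ between eligible patients and there is something to select on.

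The Data analysis section plans chi-square or Fisher tests, analysis of variance and Kruskal-Wallis tests, and names no covariates. Adding recorded covariates such as EuroSCORE II would address only what was measured, not a clinician's unrecorded impression.

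A lesser matter concerns ascertainment. The random number goes on the form that also carries the study data, and so do protocol deviations. Several components of the two primary endpoints depend on judgment: suspected respiratory infection and changed sputum in Table 1, dry cough and dyspnea in Table 2. In Table 2 only atelectasis and pneumonia call for two independent experts. If the data collector learned the arm, these items would be exposed.

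**Working it through.** **Step 1. What the assigning investigator must know.** The text gives one person four tasks: grouping, consent, determining the random number, and passing on the treatment. The last two require both the number and its link to the arm. The only source named is the Excel table. No independent list holder, sealed envelope or central service is mentioned.

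**Step 2. What the order of events protects.** The number is determined after the patient qualifies, and that order is correct. There are two cases:
- Upcoming entries are hidden from him: the order is enough, and the arm is unknown when the patient is approached.
- Upcoming entries are visible: the order gives no protection, because the next arm is known before the visit.

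The protocol does not say which case applies, so the procedure as written permits the second.

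**Step 3. The CRF.** Two statements are set side by side: the random number and deviations are entered on the CRF, and the data collector is unaware of treatment. They are compatible if the data collector has no key and the number does not openly encode the arm. Neither condition is stated. The variables listed under Data collection do not include the arm or the ventilator settings during bypass; the FiO2 listed is that at three ICU time points. The remaining route is a deviation note describing ventilation during bypass, which could show the arm in the patients who have one.

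**Step 4. Illustration of scale.** The plan gives no figure for this, so nothing of its own is to be reproduced. Inputs:
- 140 per arm = 420/3 (Sample size section).
- Baseline risk 25%, the incidence of pulmonary complications quoted in the Background.
- No treatment effect, and selective enrollment raising the risk in one arm by *s*, with the other two unchanged. The values of *s* are assumptions with no source in the protocol.

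For the three-group chi-square test (2 df, alpha 0.05, critical value 5.991), the noncentrality is

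λ = n Σ(pᵢ − p̄)² / [p̄(1 − p̄)], with p = (0.25, 0.25, 0.25 + s).

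| s | p̄ | Σ(pᵢ − p̄)² | λ | Rejection probability |
|---|---|---|---|---|
| 0.03 | 0.2600 | 0.000600 | 140 × 0.000600 / 0.1924 = 0.437 | 8.4% |
| 0.05 | 0.2667 | 0.001667 | 140 × 0.001667 / 0.1956 = 1.193 | 15.0% |
| 0.08 | 0.2767 | 0.004267 | 140 × 0.004267 / 0.2001 = 2.985 | 32.0% |

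A simulation of 200,000 runs gave 8.4%, 14.9% and 31.8%, and 5.0% with no shift. These figures concern selective enrollment only and say nothing about the CRF.

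**The case against.** The best defense is that the protocol does not describe a breach. Consent and qualification come before the number, and no recruitment step is shown being taken with the arm known. Most eligibility criteria are objective (age, pregnancy, type of surgery, hormone use of at least three months), which leaves little room to bend eligibility. The figures and the SPIRIT checklist are not available here and may describe concealment.

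This rules out several stronger readings that a reader might infer:
- *That he holds the random list.* This is a reasonable inference from his grouping role, but the text does not say it.
- *That he judges eligibility.* The sentence is in the passive and names no one.
- *That allocation is shown to be unconcealed.* The supportable statement is that no concealment mechanism is described.
- *That the data collector is unblinded by the CRF.* A random number reveals the arm only to someone with the key, or if the code is transparent. The protocol states neither, and it declares the data collector unaware. The example of an intraoperative event that it gives, a pleural incision, does not reveal the arm.
- *That the false-positive figures measure bias in this trial.* They presuppose that risk was successfully steered into one arm.

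What the defense does not answer is the combination of roles. Objective eligibility criteria do not limit discretion over whom to approach or when. The protocol assigns consent and allocation to one person and states no barrier between them. This goes beyond a detail that a statistical analysis plan would supply: the allocation procedure belongs in the protocol, and the one stated there is weaker than a readily available alternative.

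**Conclusion.** The concern holds in this form: the person who obtains consent also determines the random number and communicates the treatment, with no described safeguard against seeing the next assignment. This leaves enrollment open to selection bias that analysis could not fully remove. The conclusion rests on the stated roles and on the absence of any concealment mechanism from the text available.

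The size of any bias in this trial is unknown. The values of 8%, 15% and 32% follow only from assumed risk shifts of 3, 5 and 8 points at a 25% baseline with 140 per arm.

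The CRF matter is secondary. It is a possible leak that a short statement can close, not a contradiction of the declared blinding.

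**What to change.** Rewrite the Randomization/Blinding section as follows.

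1. The random list is prepared and kept by an existing department member who does not recruit.
2. Assignments are placed in sequentially numbered, opaque, sealed envelopes. The anesthesia provider, who has to learn the arm in any case, opens the envelope only after consent and eligibility are recorded. The recruiting investigator then has no need to know the number or the arm.
3. The key linking number to arm, and any deviation note that would reveal the arm, are kept from the data collector until database lock. Withholding the key deals with the random number, so that number may stay on the CRF.

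If concealment of this kind is already in use, the sponsor need only describe it.

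The cost is one revised section, a set of envelopes, a small amount of preparation by a colleague, and separate filing of the key and of the few revealing notes. Treatment, endpoints and sample size are unchanged.
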